## 6.6. Outcomes

### *Effectiveness*

Main outcome: time (days) from intubation to extubating.

- Secondary outcomes:

- Days free of mechanical ventilation until day 28
- Days of delirium until day 28
- Time in ICU with delirium until day 28
- Days of hospitalization with delirium until day 28
- Days of sedation until day 28
- Sedation-free days until day 28
- Extubating failure
- Need for non-invasive mechanical ventilation
- Exploratory outcomes:
- Barthel index at discharge
- Days of hospital stay
- Length of stay in ICU
- Mortality from any cause up to 90 days
- Time from intubation to start of therapy
- Muscular strength measured with the Medical Research Council (MRC) scale
- Dysphagia 72 hours after extubation
- Dysphonia 72 hours after extubation
- Time until initiation of oral administration post-extubation
- Development of healthcare-associated pneumonia,
- Maximum mobility measured by JH-HLM
- Grip strength
- Cognitive function measured using the Montreal Cognitive Assessment (MOCA)
- Evaluation of functionality in daily activities until day 28
- Quick sensitivity and dexterity test

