## 6.7. Measurements

Within the framework of the protocol, measurements will be conducted at six key moments of the research: upon admission to the intensive care unit, during observation in the intensive care unit, at the start of ventilatory support weaning, post-extubation, upon hospital discharge, and at the end of the observation period. Additionally, continuous measurements of outcomes associated with the safety of the intervention will be performed.

Upon admission, crucial details about each patient will be collected, such as name, identifier code, medical record number, sex, and ethnicity. Health and functionality aspects will also be evaluated, including the Barthel Index and Body Mass Index. Diagnostic information will be complemented with the ICD-10 code, study group (early vs. late), and the unit of admission (surgical, neurological, septic and respiratory, cardiovascular, or burn unit). Severity scores such as SOFA, APACHE II, and SAPS II will be incorporated, along with temporal data such as admission date, discharge date, and the time elapsed from intubation to the start of therapy. Regarding respiratory parameters, fundamental variables at the time of intubation will be detailed, such as tidal volume, respiratory rate, PEEP, plateau pressure, static lung compliance, driving pressure, airway resistance, and the PaO2/FIO2 ratio.

During the observation phase, a rigorous daily patient evaluation process will be implemented to ensure accurate recording of their progress. Key variables will be monitored, such as days on mechanical ventilation (recording start and end dates), ventilator-free days, days with delirium (indicating start and end dates), days of hospitalization with delirium, and days of sedation (with details of start and end dates). The duration of mechanical ventilation, the possible need for tracheostomy, the presence of adult respiratory distress syndrome, and the eventual occurrence of healthcare-associated pneumonia will also be documented.

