1. Oxygenation (O): The PaO2/FiO2 ratio > 150, arterial oxygen saturation > 90% with FIO2 0.4, PEEP ≤ 8 cm H2O and Tobin's index (fr/Vt) < 105. Each variable will be marked as yes or no.
2. Respiratory Mechanics (M): exhaled tidal volume greater than 5 ml/kg vital capacity > 10 ml/kg, maximum inspiratory pressure (MIP) ≤ -20 to 25 cmH2O, respiratory rate < 35 per minute, and values of PIM and PEM.
3. Acid-Base (A): paCO2 < 50 mmHg, pH > 7.32, lactic acid > 2, and venous saturation > 75%.
4. Hemodynamic (H): Systolic pressure > 90 or < 160, heart rate ≤ 140 per minute, the presence of arrhythmias and doses of vasopressors (high > 0.2 mcg (kg/min)
5. Airway (A): history of difficult airway and leak test results > 40%.
6. Clinical Component (+): Additional clinical factors, such as the presence of effective cough, management of secretions, the patient's neurological status, resolution of the underlying cause of intubation, and the manifestation of clinical signs of respiratory distress, as well were considered.

After extubation, several indicators will be carefully monitored to assess the patient's recovery and stability. The presence of dysphonia at 72 hours, maximum mobility measured by JH-HLM at 24 hours, and grip strength within the same period will be recorded. Additionally, the need for non-invasive mechanical ventilation at 48 hours will be evaluated, indicating whether it is required or not. The possible presence of dysphagia at 72 hours will also be documented, along with the timing of oral intake initiation, classified into two options: 1) between 12 and 24 hours, and 2) after 24 hours. The occurrence of extubation failure at 48 hours will be recorded, indicating whether

it occurred or not, and muscle strength will be measured using the MRC Scale at 24 hours to assess the patient's functional capacity after the extubation procedure.

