|                                          | maintain sustained attention, disorganization of thought, or fluctuating changes in level of consciousness).                   |                       | 4. Fluctuating changes in level of consciousness (+/-) |
| Days of delirium                         | Days with the presence of delirium                                                                                             | Discrete Quantitative | Days                                                   |
| Sedation days                            | Days with sedation                                                                                                             | Discrete Quantitative | Days                                                   |
| Sedation-free days                       | 28 days fewer days of sedation                                                                                                 | Discrete Quantitative | Days
It will be defined as 0 if the patient dies.   |
| Barthel index at hospital discharge      | The Barthel Index is a scale used to measure a person's degree of functional independence in activities of daily living (ADL). | Discrete Quantitative | It will be 0 if the patient dies.                      |
| Days of hospital stay                    | Days of hospital stay                                                                                                          | Discrete Quantitative | Days                                                   |
| Days of ICU stay                         | Days of ICU stay                                                                                                               | Discrete Quantitative | Days                                                   |
| Mortality                                | Death                                                                                                                          | Qualitative Nominal   | Yes or no                                              |
| Time from intubation to start of therapy | Time from intubation to start of therapy                                                                                       | Discrete Quantitative | Days                                                   |

Association between early multimodal therapy and days of mechanical ventilation in the intensive care unit of the Fundación Santa Fe de Bogotá: A randomized controlled clinical trial.

Version 6.0

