#### During observation:

To register of shape suitable for these data must pass all the days to appreciate the patient.

- Days of Mechanical Ventilation: \_\_\_\_\_ (date of start-end date)

- Days Free from Mechanical Ventilation: \_\_\_\_\_(calculated the final of the observation)
- Days of Delirium: \_\_\_\_\_( start date - end date)
- Days of Hospitalization with Delirium: \_\_\_\_\_(calculated the final of the observation)
- Sedation Days: \_\_\_\_\_(date of start- date of ending)
- Days Free from Sedation: \_\_\_\_\_(calculated the final of the observation)
- Prolonged Mechanical Ventilation: \_\_\_\_\_(Yes/No)
- Tracheostomy: \_\_\_\_\_(Yes/No).
- Syndrome of Difficulty Respiratory of the Adult: \_\_\_\_\_(Yes/No)
- Presence of pneumonia associated with the Careful of health: \_\_\_\_\_(Yes/No)
- Need dialysis: \_\_\_\_\_(Yes/No)
- Medium with norepinephrine \_\_\_\_\_(Yes/No)
- Support with vasopressin \_\_\_\_\_(Yes/No)
- Medium with inotrope \_\_\_\_\_(Yes/No)
- Dose maximum of norepinephrine \_\_\_\_\_( mcg /kg/min)
- Maximum dose of vasopressin \_\_\_\_\_(IU/min)

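### Time to oral intake has no code for a start before 12 hours or for no start, and single start–end dates for delirium and sedation can overcount days if episodes recur

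*Protocol*

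**What the plan says.** **Oral intake.** Section 6.6 names the outcome "Time until initiation of oral administration post-extubation" and places it among the exploratory outcomes; the PICOT table in Section 3 lists it as secondary. Section 6.7 says the timing will be "classified into two options: 1) between 12 and 24 hours, and 2) after 24 hours". The variable table in Section 6.11 gives the same two codes and types the variable as qualitative nominal. The post-extubation part of the Annex 5 form repeats them.

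**Delirium and sedation.** The variable table defines days of delirium as "Days with the presence of delirium", defines sedation days in the same manner, and sets sedation-free days at 28 minus sedation days (0 if the patient dies). Section 6.7 promises that "a rigorous daily patient evaluation process will be implemented to ensure accurate recording of their progress", then lists "days with delirium (indicating start and end dates), days of hospitalization with delirium, and days of sedation (with details of start and end dates". The observation part of Annex 5 has one blank for days of delirium, annotated "start date - end date", and one for sedation days, annotated "date of start- date of ending". Days of hospitalization with delirium and sedation-free days are to be calculated when observation ends. The form has no daily delirium or sedation entry and no row for a second episode.

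**The concern.** Both issues concern data capture. A later analysis plan cannot restore hours or daily states that were never entered.

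For oral intake, an outcome named as a time is stored in two classes that do not cover all patients. Speech therapy in the intervention works on the muscles and reflexes of swallowing (Section 6.5), so early starters are of direct interest, and they have no code.

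For delirium and sedation, the definition is a count of affected days but the form takes one interval. If a patient has two episodes and staff enter the first start and the last end, the free days between them are counted as affected. Any such error passes into every outcome derived from these fields.

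**Working it through.** The plan states no figure on this point, so there is none to reproduce. The check compares the outcome list, the measurement text, the variable table and the form.

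**1. Oral intake.** Split the N extubated patients into *a* (start before 12 h), *b* (12–24 h), *c* (after 24 h) and *d* (not started).

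- Valid codes exist for *b* and *c* only, so the share without a code is (a + d)/N.
- No document gives *a*. If 10–30% start before 12 h (assumption), then with 37 per arm, all extubated, that is 0.10 × 37 = 3.7 to 0.30 × 37 = 11.1, or about 4 to 11 patients per arm, before adding *d*.
- The true proportion started by 24 h is (a + b)/(a + b + c + d). If staff put *a* under the first code and *d* under the second, this proportion is unchanged and only detail is lost. If *a* is left blank, it becomes b/(b + c + d), which is lower whenever *a* and c + d are above zero. The effect on the comparison depends on *a* in each arm and on how the gap is handled.

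**2. Delirium and sedation: count against span.** Span = last day − first day + 1.

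| Affected days | Count | Span | Excess |
|---|---|---|---|
| Delirium 3, 4, 9 | 3 | 9 − 3 + 1 = 7 | 4 |
| Delirium 3, 4, 5 | 3 | 5 − 3 + 1 = 3 | 0 |
| Sedation 1, 2, 3, 10 | 4 | 10 − 1 + 1 = 10 | 6 |

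Sedation-free days in the last row: 28 − 4 = 24 by count, 28 − 10 = 18 by span. The protocol does not say whether both end dates count. Plain subtraction would give 9 − 3 = 6 in the first row and 5 − 3 = 2 in the second.

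**3. Possible size in a group.** A small on/off simulation used only assumed inputs: 20,000 patients per setting, each affected on the first day, and a daily chance of 0.5 or 0.7 that an episode continues. Ratio of mean span to mean count:

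| Window (days) | No relapse | Daily relapse chance 0.1–0.3 |
|---|---|---|
| 7 | 1.00 | 1.18–1.52 |
| 10 | 1.00 | 1.37–1.80 |
| 14 | 1.00 | 1.58–2.15 |

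**4. Reach.** Of the eight secondary outcomes in Section 6.6, three concern delirium (days, time in ICU, hospital days) and two concern sedation (days, sedation-free days). That makes five dependent on the two fields. Time in ICU with delirium has no row of its own in the variable table and no field in Annex 5.

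**The case against.** The strongest reply is that no text sets days equal to end minus start or limits entry to one episode. The definitions count affected days, and Section 6.7 and Annex 5 call for the patient to be seen daily. Start and end dates can also be entered for several episodes, and Section 6.11 places data capture in REDCap, whose layout may differ from Annex 5. This stands as far as it goes: a single interval is a fair inference from the form, but it is not a stated rule. It does not remove the mismatch, because the form shown has nowhere to store each day's result.

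A reader might infer more than the documents support:

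- **That recurrence is documented.** The item "fluctuating changes in level of consciousness" is a CAM-ICU criterion that counts towards delirium being present; it does not say that delirium clears for days and returns. The clause on temporary interruption in Section 6.7 concerns multimodal therapy, not sedation.
- **That ICU delirium cannot be separated from ward delirium.** With one unbroken episode, the delirium dates and the stay data allow the ICU part to be derived. The difficulty arises only with separate episodes.
- **That the oral-intake gap biases towards no effect.** Step 1 of the working shows that the direction depends on how uncoded patients are entered.
- **That the error must differ between arms when stay differs.** It also requires recurrence, for which the protocol gives no rate.

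**Conclusion.** The oral-intake defect is firm. The same two codes appear in all three places and leave out starts before 12 h and patients who never start. The number affected is unknown; the 4 to 11 per arm rests on the assumed 10–30%.

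The delirium and sedation point holds as a risk: the capture does not match the definition, and five of the eight secondary outcomes depend on it. Inclusive counting gives no error for one continuous episode. With recurrence and use of the span, the examples show 4 extra delirium days and 6 extra sedation days, and the assumed simulation settings give about 1.2 to 2.2 times the true count. It would go too far to say that these outcomes are mis-measured, because that needs both recurrent episodes and a span calculation, and the protocol states neither. The primary outcome is not affected by either issue.

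**What to change.** - **Oral intake:** record the date and time of first oral intake after extubation, or that it was not started, and derive hours. If categories are kept, add one for under 12 h and one for not started. Align Section 6.7, the variable table and Annex 5, and give the outcome the same tier in Sections 3 and 6.6.
- **Delirium and sedation:** in Annex 5 and REDCap, replace the single date pair with a daily yes/no for each to day 28, with location (ICU or ward). Repeatable episode rows, with location and a stated rule for counting the end dates, would also serve. State in the variable table that the outcomes are the number of days present, and add a row for time in ICU with delirium.

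The cost is a few more entries per patient. In the ICU they use the daily evaluation already planned. Section 6.7 describes observation in the ICU, so the team should confirm how delirium is assessed on ward days up to day 28; the hospital-days outcome already depends on that.

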In the weaning initiation phase, attention will focus on a series of key parameters to assess the patient's ability to discontinue mechanical ventilation. Detailed data will be recorded, such as the Delta POCC, reflecting the variation in vital capacity during a cough cycle, muscle pressure, P0.1 representing the pressure in the first 0.1 seconds of inspiration, the amount of secretions through the orotracheal tube, the asynchrony index, negative inspiratory force (NIF), leak percentage, peak cough flow, and specific measurements related to diaphragmatic capacity, such as excursion and thickness. These data provide a comprehensive view of respiratory functionality during the weaning

**Association between early multimodal therapy and days of mechanical ventilation in the intensive care unit of the Fundación Santa Fe de Bogotá: A randomized controlled clinical trial.**

Version 6.0

Fundación Santa Fe de Bogotá

April 8, 2024

process, allowing informed decision-making about the feasibility of withdrawing mechanical ventilation.

Before the extubation process, critical data will be collected to assess the patient's readiness and minimize potential risks. The Delta POCC, muscle pressure, P0.1, the number of secretions through the orotracheal tube, the asynchrony index, NIF, leak percentage, peak cough flow, diaphragmatic excursion, and thickness will be recorded. Additionally, the OMAHA score at the time of extubation will be documented, indicating the presence or absence of this event.

The decision to extubate a patient, according to the OMAHA+ Scale, is based on a comprehensive evaluation of various clinical parameters. Each component of this scale provides crucial information about the patient's ability to tolerate the withdrawal of ventilatory support. When all factors described in the OMAHA+ Scale are present, extubation is performed.

The systematic application of the OMAHA+ Scale is fully standardized in our unit, forming an essential part of our extubation protocol. This ensures a thorough and uniform evaluation of patients before withdrawing ventilatory support. Additionally, we have implemented a systematic review procedure of the process to strengthen the consistency, accuracy, and quality of our clinical practice.

The OMAHA+ Scale is detailed below:

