| Dysphonia at 72 hours.       | Presence of dysphonia 72 hours after extubation.                                                                  | Qualitative Nominal | 0: No
1: Yes                                                                                                                                                                                                                                    |
| OMAHA+                | The use of the OMAHA+ Scale during the process of withdrawing ventilatory support to make the extubation decision | Qualitative Nominal | NOT = 0
Yes = 1                                                                                                                                                                                                                                 |
| Alteration in blood pressure | The patient experiences significant changes in blood pressure during the therapies                                | Nominal qualitative | 0 = No

1 = Hypotension without the requirement for medical management

2 = Hypotension requiring medical management

3 = Hypertension without requiring medical management

4 = Hypertension requiring medical management |
| Cardiac arrhythmias          | The patient had a cardiac arrhythmia during therapy.                                                              | Nominal qualitative | 0 = No

1 = Cardiac arrhythmia without a requirement for medical management

2 = Cardiac arrhythmia requiring medical management                                                                                                       |
| oxygen desaturation          | The patient became desaturated during therapy                                                                     | Nominal qualitative | 0 = No

1 = Oxygen desaturation without requirement for medical management                                                                                                                                                                   |

|                         |                                                                                 |                     |                                                                                                                                                    |

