Diaphragmatic dysfunction and ICU-acquired weakness impact success or failure in weaning from mechanical ventilation according to measurements guided by ultrasonographic evaluation of the diaphragm: excursion and measurement of diaphragmatic thickness; as well as muscle strength according to the MRC scale in a spontaneous breathing test (PVE) for 30 minutes, this is how a study evaluated these variables, finding that weakness acquired in the ICU was directly related to difficult and prolonged weaning, longer stay in ICU and prolongation of mechanical ventilation. (3)

The ventilatory weaning process is a term used to describe the gradual process of decreasing ventilatory support, progressively decreasing parameters until the patient can start breathing with minimal ventilatory support required. There is a classification of ventilatory weaning divided according to PVE: Simple weaning, is the first successful spontaneous breathing test. Difficult weaning failed PVE on the first or third attempt or required PVE after seven days of mechanical ventilation and

prolonged weaning, in which the patient presents successful PVE in a time greater than seven days under ventilatory support.

There are risk factors for extubation failure:

- Failure of two further tests of ventilation spontaneous
- Insufficiency cardiac chronicle
- Cough weak
- Risk of stridor post extubation
- Age > 65 years.
- PaCO2 > Four. Five mmHg later to the extubation. (4)

It has recently been shown that the spontaneous breathing test (SVT) in PSV for 30 minutes resulted in a significantly successful extubation rate relative to the T-Tube test for 2 hours, given that a less demanding test vs. a much longer time may overestimate the inspiratory effort after extubation. (5)

Hemodynamic monitoring is also crucial for extubation success or failure and is the linear relationship between the dose of vasopressor support and the risk of extubation failure. Vasopressor doses > 0.1 mcg/kg/min have been associated with the risk of intubation about fluid balance and filling pressures, since by having low doses of vasopressor support the urinary balance will tend to be negative to avoid overload. Volume and subsequent pulmonary edema. (6)

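### The written OMAHA+ extubation rule has a systolic pressure limit that no value can fail and a lactate limit that apparently points the wrong way

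*Protocol*

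**What the plan says.** Section 6.7 (Measurements) describes how the extubation decision is made and gives the rule: "When all factors described in the OMAHA+ Scale are present, extubation is performed". It says the scale is standardized in the unit and then sets out its components. Two of them matter most here.

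- Acid-base: arterial CO2 below 50 mmHg, followed by "pH > 7.32, lactic acid > 2, and venous saturation > 75" per cent.
- Haemodynamic: "Systolic pressure > 90 or < 160, heart rate ≤ 140 per minute", followed by "the presence of arrhythmias and doses of vasopressors (high > 0.2 mcg (kg/min".

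The airway component includes "history of difficult airway". The clinical component ends with "and the manifestation of clinical signs of respiratory distress".

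The variable table in section 6.11 confirms that the scale is meant to drive the decision. It defines the OMAHA+ variable as "The use of the OMAHA+ Scale during the process of withdrawing ventilatory support to make the extubation decision".

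The main outcome in section 6.6 is the time in days from intubation to extubation. In section 6.13, extubation (yes/no) combined with ventilation time forms the dependent variable of the Cox regression.

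**The concern.** The rule is a conjunction: every listed factor has to be present. A wrong item therefore has one of two consequences. It may exclude nobody and do no work, or it may exclude the wrong patients. The systolic item appears to do the first and the lactate item the second.

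Two things are at stake. One is reproducibility. Section 6.1 says participants and researchers cannot be blinded, and the main outcome ends with a clinician's decision. A clear written rule is one of the main protections for such an outcome, and a rule that cannot be followed literally leaves the decision to unwritten judgement. The other is patient safety, because these are readiness criteria for removing an airway. Section 6.11 adds that investigators' knowledge of the protocol is examined, so staff are trained on this text.

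**Working it through.** The plan gives no figure to reproduce. The check is whether the written inequalities can do what the rule asks of them.

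**Inputs**, all from Protocol section 6.7: the all-factors-present rule; systolic pressure above 90 or below 160; lactate above 2, with no unit; and the neighbouring acid-base limits (CO2 below 50 mmHg, pH above 7.32, venous saturation above 75%).

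**Systolic pressure as written: (SBP > 90) or (SBP < 160).** To fail, a value must be at most 90 and at least 160 at once, which is impossible.

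- SBP 70: above 90 is false, below 160 is true, so it passes.
- SBP 200: above 90 is true, below 160 is false, so it passes.
- Of the 301 whole numbers from 0 to 300 mmHg, 301 pass.

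**Systolic pressure with both limits required: (SBP > 90) and (SBP < 160).** Both 70 and 200 fail. Whole-number passes run from 91 to 159, that is 159 − 91 + 1 = 69 values.

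**Lactate, as written and with the presumed correction:**

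| Lactate | As written (> 2) | Presumed (< 2) |
|---|---|---|
| 0.8 | fails | passes |
| 1.0 | fails | passes |
| 1.5 | fails | passes |
| 2.0 | fails | fails |
| 2.1 | passes | fails |
| 3 | passes | fails |
| 4 | passes | fails |
| 8 | passes | fails |

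The other three acid-base items each name the side on which a patient is fit for extubation. Lactate above 2 names the opposite side. Read literally under the all-factors rule, a patient with lactate of 2 or below never qualifies, while lactate 8 with systolic pressure 70 satisfies both of these items. No other part of the protocol gives a different lactate or systolic threshold for extubation.

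**Items without a direction.** Arrhythmias, vasopressor dose, difficult airway and respiratory distress are adverse findings or matters to assess. Requiring them all to be present makes no clinical sense, and the text does not say what result is needed. For vasopressors it flags a high dose (above 0.2), whereas the respiratory therapy justification in Annex 1 describes "the linear relationship between the dose of vasopressor support and the risk of extubation failure". This is a gap in wording, distinct from the two wrong thresholds.

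**The case against.** The strongest reply is that nobody could apply the list literally. It would require arrhythmias and respiratory distress before extubation, so it evidently mixes pass criteria with items to assess and record. Section 6.7 calls the scale already standardized in the unit, and the mechanical ventilation standard in Annex 1 refers to a separate institutional extubation standard. The English text has many visible translation slips, and the intended systolic range is obvious to an intensivist. The thresholds are not analysed either: the variable table records only whether the scale was used, Annex 5 records only a plus or minus at extubation, and the Cox event is extubation whenever it occurs. A patient with lactate 8 and systolic pressure 70 would still have to meet the remaining criteria.

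Much of this stands. A translation or transcription slip is likely, and the bedside form is probably correct and used equally in both arms. The link to the analysis is indirect, and those two items alone would not send such a patient to extubation. The protocol has no lactate reference range, so the direction of that error is inferred from the neighbouring items and the clinical meaning of a raised lactate.

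The reply does not rescue the text. Nothing marks the two numeric limits as assess-only. They stand among pass criteria, and section 6.7 makes the presence of all factors the trigger. The protocol presents this list as the scale itself, and a monitor, ethics committee or replicating site that relies on the protocol has nothing else to go by.

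**Conclusion.** The point holds and should be fixed. Two thresholds in the written rule for extubation are wrong as stated. The systolic error is a matter of logic and is certain. The lactate error is apparent: it rests on the all-factors rule, on the direction of the three neighbouring criteria and on what a raised lactate means clinically. The adverse items without a direction are a lesser wording gap.

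The size is confined to which patients meet the written rule. The systolic item excludes no value, where the evident intention admits 91 to 159 mmHg. The lactate item fails 1.5 and passes 8, and the presumed correction reverses both. No directional bias between arms and no effect on ventilation days is claimed.

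**What to change.** Check the list in section 6.7 against the unit's approved OMAHA+ form and then:

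1. Write the systolic item as above 90 **and** below 160 mmHg.
2. Correct the lactate item, presumably to below 2, and give its unit. The form should settle how a value of exactly 2 is treated.
3. Reword the trigger so that extubation requires all criteria to be met, in place of all factors being present.
4. Mark arrhythmias, high vasopressor dose, difficult airway and respiratory distress either as required to be absent or as assess-only.

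The cost is protocol wording only. No new data field is needed, and neither the design nor the sample size changes.
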